#### Procedure for unblinding if needed {17b}

Not applicable, care providers are not blinded to intervention assignment.

### Data collection and management

#### Plans for assessment and collection of outcomes {18a}

##### Screening period

The day before surgery, an initial screening will be performed by the participating investigator ([name]) based on the surgery request form, and for each recipient who passes the initial screening, the investigator should fully inform him/her of the purpose, steps, potential benefits, and risks of this study. After obtaining the participant’s signed informed consent, further screening is performed according to the inclusion/exclusion criteria and the following information is collected:Record of signing the informed consentSigned informed consent formDemographic data: age, sex, height, weight, and body mass index (BMI)Medical history and related information: diagnosis (indications for liver transplantation), comorbidities, previous and current glycemic control, as well as history of medication, lifestyle interventions, smoking, alcohol consumption, food and drug allergies, and surgical anesthesiaLaboratory tests: preoperative HbA1C, liver function, kidney function, blood routine, and coagulation testsOther examinations: electrocardiogram, ultrasonic cardiogram, carotid artery ultrasound, and abdominal CTDonor information: age, height, weight, BMI, cause of death, liver biopsy, and virological findings

*Intervention period*
Randomized recordingBlood glucose: blood glucose, number of arterial blood gas checks, insulin and glucose administration (frequency and doses)Surgery: length of surgery, surgical method, length of anhepatic phase, warm ischemia, and cold ischemia timeAnesthesia: duration of anesthesia, intraoperative drug use (drug name and dose used), blood pressure, cardiac output, stroke volume variation, body temperature, and BIS

##### Follow-up period

Patients were followed up on postoperative days 1 to 7 and days 15, 30, 60, and 90. Follow-up will be conducted by the investigator in the ICU or general ward during hospitalization and by telephone after discharge, respectively. The following information will be collected during the follow-up period:Incidence of SSIsIncidence of other infections: abdominal, pulmonary, and urinary tract infectionsPostoperative liver function: liver function and coagulation tests on postoperative days 1–7Incidence of MACE: cardiovascular death, myocardial infarction, and strokeLength of postoperative ICU stay and hospitalizationAll-cause mortality within 30 daysRe-hospitalization rate within 90 daysSecondary transplantation rate within 90 days

#### Plans to promote participant retention and complete follow-up {18b}

The investigator will explain to patients the importance and specific arrangements for completing follow-up visits on time and will encourage patients to complete them throughout the trial. Patients may withdraw from the trial at any time during the follow-up period without giving a reason. The investigator will perform complete-case analysis for all the outcomes. If more than 5% of the data are found to be missing for the primary outcome, a sensitivity analysis will be performed using multiple imputation.

#### Data management {19}

Data management for the study is performed by separate investigators for raw data management, case report form (CRF) design, data archiving, and storage management of the clinical and specimen information database.

CRF design and recording: we designed a CRF based on standard metadata. Investigators should record the original observations to the paper CRF in a timely, complete, and accurate manner.

Data archiving: The clinical information data of patients are systematically summarized and organized on an individual case basis with a timeline. After the CRFs are completed and signed by the investigator, two other investigators who are blinded to treatment assignment will use the EpiData 3.10 database system for data entry and management. All data files are transferred out to SPSS files at the end of the study and then statistically analyzed.

#### Confidentiality {27}

The electronic data in this study will be managed by dedicated personnel. The personal patient information will be appropriately hidden, only study-related data will be retained for statistical analysis. All CRF will be placed in a locked cabinet and managed by dedicated personnel. Researchers should follow professional confidentiality rules and must keep all personally identifiable information of patients as well as medical information confidential. At the end of the submission, paper CRFs are placed in a special locked cabinet and stored for 3 years before destruction, and electronic data are stored encrypted after hiding patients’ personal information. All work is assigned to a dedicated person.

#### Plans for collection, laboratory evaluation, and storage of biological specimens for genetic or molecular analysis in this trial/future use {33}

In this study, blood samples will be collected from patients for intraoperative arterial blood gas analysis, with the number of collections depending on the length of the procedure and changes in blood glucose. Patient blood is collected once a day for 7 days postoperatively for liver function and coagulation tests. Collected blood specimens will be disposed of at the end of the study.

### Statistical methods

#### Statistical methods for primary and secondary outcomes {20a}

Continuous variables such as CV%, mean blood glucose, and liver transaminases levels and other indicators will be tested for normality using Kolmogorov–Smirnov test. Measures satisfying normal distribution will be expressed as mean ± standard deviation, and median (interquartile range) when data are not normally distributed. Qualitative data such as the incidence of hypo/hypoglycemia, SSIs, and MACE will be expressed as frequencies (percentages).

Normally distributed data will be compared between two groups using *t*-test, multiple groups will be compared using ANOVA, and non-normally distributed data will be compared using Mann–Whitney *U*-test. The chi-square test will be used for comparison between groups for numerical data. Comparisons of CV%, the primary outcome, will be made using either the *t*-test or the Mann–Whitney *U* test.

Repeated measures will be compared using analysis of variance (ANOVA). Blood glucose analysis will be performed using multifactorial analysis.

In this study, the accuracy of CGM monitoring will be tested simultaneously for patients in the CG group. Pearson linear correlation analysis will be applied to determine the correlation between CGM- and ABG-derived glucose levels; Clarke error grid analysis will be used to evaluate the consistency between CGM- and ABG-derived glucose levels. The formula: [ABG glucose − CGM glucose)/ABG glucose] × 100% will be applied to calculate the overall clinical mean relative error. If this error value is ≤ 17% and the sum of the data falling in areas A and B in the Clark error grid analysis is not less than 95% of the total, the accuracy will be judged to be satisfactory.

All analyses will be performed using SPSS 26.0 (SPSS, USA) and STATA 14.0 (StataCorp LP, College Station, TX).

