#### Secondary outcomes

This study intends to further assess the effectiveness of CGM-based intraoperative glucose management in LT by mean intraoperative glucose values, as well as rates of hypoglycemic events and hyperglycemic events. The accuracy of CGM for intraoperative glucose monitoring will be evaluated by overall clinical mean relative error and Clarke error grid analysis. The safety of CGM for intraoperative glucose monitoring will be evaluated by the incidence of severe adverse reactions (SAEs).

Additionally, this study intends to evaluate the prognostic improvement of patients with different glucose monitoring modalities by comparing the incidence of SSIs, other infections, postoperative liver function, and major adverse cardiovascular events (MACE) in the two groups at 3 months postoperatively.

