#### Methods in analysis to handle protocol non-adherence and any statistical methods to handle missing data {20c}

All randomized participants will be included in the main analyses. An intention-to-treat analysis will be carried out relating to any protocol non-adherence or dropouts. Per-protocol dataset will also be performed for any of the missing data. Besides, we anticipate little loss to follow-up for the primary outcome. Nevertheless, if there is more than 5% missing data for the primary outcome, we will perform a sensitivity analysis using multiple imputations for the missing data.

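### Repeated measures go to ANOVA and all outcomes to complete cases; applied to daily liver function on days 1-7, a patient with one missing day drops out, and no remedy is planned

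*Protocol article*

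**What the plan says.** All references are to the protocol article.

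- **Method.** Statistical methods {20a} says "Repeated measures will be compared using analysis of variance (ANOVA"). It names no outcome. Blood glucose has a separate sentence that assigns it a multifactorial analysis.
- **Missing data.** The retention section {18b} says "The investigator will perform complete-case analysis for all the outcomes". The only other measure is for the primary outcome. In {20c}: "if there is more than 5% missing data for the primary outcome, we will perform a sensitivity analysis using multiple imputations".
- **Analysis set.** {20c} also says "All randomized participants will be included in the main analyses", under intention to treat. The criteria for removal from the trial include death in the first three months after transplantation.
- **Outcome.** Secondary outcomes lists "comparing the incidence of SSIs, other infections, postoperative liver function, and major adverse cardiovascular events (MACE) in the two groups".
- **Schedule.** The follow-up section plans "liver function and coagulation tests on postoperative days" 1 to 7, and {33} confirms: "Patient blood is collected once a day for 7 days postoperatively for liver function and coagulation tests". Re-transplantation within 90 days is recorded. No rule is given for liver values obtained after it.

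**The concern.** The protocol makes two definite choices here, so this is not a detail left to an analysis plan. Together they give a weak analysis of a seven-value series. Classical repeated-measures ANOVA needs every planned value, and its univariate form also assumes a common correlation pattern between days. A patient with six of seven values contributes nothing.

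Two things are at stake. The first is precision, because observed days are thrown away. The second is possible bias in the comparison of arms. If days are missing because the patient was doing badly, the patients who remain are a healthier selection, and the selection may differ between arms. A patient who dies on day 5 would lose the four values already recorded.

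**Working it through.** **Inputs.** From the document: seven planned daily values, 90 patients per arm (180 in all), ANOVA, complete cases. The document gives no missing rate, standard deviation or expected difference for liver function, so there is no figure of its own to reproduce on this point. All rates below are assumptions.

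**Step 1: patients lost.** If each day is missing independently with probability m, the share with all seven days is (1 - m)^7 and the share dropped is 1 - (1 - m)^7.

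| Assumed m per day | (1 - m)^7 | Dropped | Remaining of 180 |
|---|---|---|---|
| 1% | 0.932 | 6.8% | 168 |
| 2% | 0.868 | 13.2% | 156 |
| 5% | 0.698 | 30.2% | 126 |

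Under independent missingness this costs precision only.

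**Step 2: precision and bias.** A simulation used 90 patients per arm, seven days, SD 1, autoregressive correlation 0.8 between adjacent days, a true difference of -0.40 and 300 runs. All of these are assumed. It compared complete cases with a likelihood model for all observed days (arm-by-day means, unstructured covariance), which is equivalent to the mixed model proposed below.

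| Missingness | Patients complete | Full data | Complete cases | All observed days |
|---|---|---|---|---|
| 3% per day at random (day 1 always present) | 83.1% | -0.390 | -0.389 | -0.390 |
| Dropout depends on previous observed value | 82.8% | -0.391 | -0.330 | -0.391 |
| Dropout depends on unseen current value | 85.0% | -0.402 | -0.340 | -0.386 |

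- **Row 1.** Neither method is biased. The empirical SD of the estimate is 0.133 for complete cases and 0.115 for all observed days. These SDs carry simulation error of about 4% (1/sqrt(2 x 300) = 0.041). The loss of patients alone implies a variance ratio of about 1/0.831 = 1.20.
- **Row 2.** Complete cases shrink the difference by (0.391 - 0.330)/0.391 = 16%. The model on all observed days recovers it.
- **Row 3.** Complete cases shrink it by (0.402 - 0.340)/0.402 = 15%. The model shrinks it by (0.402 - 0.386)/0.402 = 4%, and its control-arm mean is still off by -0.04 SD. The repair is partial.

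**Step 3: what the model cannot reach.** Patients removed for death within three months are absent whichever model is fitted. If they are kept, the model carries their expected liver function past death. It also does not say which graft is being measured after re-transplantation.

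**The case against.** **The ANOVA sentence does not mention liver function.** {20a} lists liver transaminases among its continuous variables, with *t*-test or Mann-Whitney for two groups, and Secondary outcomes speaks of three months. If each day were tested separately on the values present, one missing day would not remove a patient from the other days. This stands: the link is an inference. It is a strong one, because the daily values on days 1-7 are the only liver-function data scheduled after surgery, and glucose is assigned another method.

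**Complete case is not defined, and {20c} includes all randomized patients.** Also true. But two sections that disagree do not supply a remedy, and multiple imputation is confined to the primary outcome.

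**The loss may be small.** At 1% per day the 6.8% is below the 10% dropout allowance in Sample size {14}. The document supports neither a low nor a high rate. Its expectation of little loss concerns the primary outcome.

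**Two stronger readings are tempting.** A reader might infer that patients whose grafts fail early are the first to be lost. The document does not show this. Follow-up is in the ICU or ward during hospitalization, with daily blood sampling, so graft failure alone does not stop the tests. Of the early events considered here, only death necessarily ends the series, and no week-1 death rate is given. A reader might also infer that a mixed model cures the problem at no cost. Rows 2 and 3 above show that this depends on why values are missing, and Step 3 shows what it leaves open.

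**Conclusion.** The point holds as a recommended change to a secondary analysis. Read together, {20a} and {18b} commit the day 1-7 liver function and coagulation data to a method that discards partly observed patients. This rests on three assumptions: that the ANOVA sentence covers these data, that the standard form of repeated-measures ANOVA is meant, and that a complete case is a patient with all seven days.

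The size is 6.8% to 30.2% of patients lost over an assumed 1% to 5% missing per day. These percentages should not be read as bias, since independent missingness produces none. Bias is possible if missing days follow poor liver function. In the assumed scenarios it shrank the arm difference by about 15%, but the document does not establish that pattern. The primary outcome is a single coefficient of variation per patient and is unaffected.

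**What to change.** Replace the ANOVA sentence with wording such as: *Daily liver function and coagulation values on postoperative days 1-7, log-transformed where skewed, will be compared with a linear mixed model containing arm, day and arm by day, with unstructured within-patient covariance, using all observed days of all randomized patients.*

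With it:

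1. Reconcile this with the complete-case rule in {18b}, the all-randomized statement in {20c} and the removal of deaths in the removal criteria. Otherwise the model is fitted to a selected set.
2. State how liver values after re-transplantation are handled in the analysis.
3. Report deaths and re-transplants in days 1-7 by arm beside the model.
4. Add one simple sensitivity analysis for early deaths and re-transplants, for example a rank comparison that places them worst.

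The cost is a few sentences, settled before unblinded data are seen. No extra patients or measurements are needed, and the packages named in {20a} ("All analyses will be performed using SPSS 26.0 (SPSS, USA) and STATA 14.0 (StataCorp LP, College Station, TX")) both fit mixed models. The downside is the missing-at-random assumption and the implicit extrapolation beyond death, which item 4 is meant to probe.

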Continuous glucose monitor (CGM) is a wearable device that automatically detects glucose levels from interstitial fluid or blood every 5 min [30, 31]. Among them, interstitial fluid CGM has been widely used in the chronic disease management of diabetic patients due to the advantages of minimally invasive, stability and less complications [32], and its related products have been approved and marketed by the National Medical Products Administration (NMA) of China. Compared with blood gas examination, CGM provides more detailed blood glucose readings. In addition, CGM evaluates GV parameters such as CV% and has gradually become the gold standard for assessing short-term blood GV in recent years [33, 34]. Given that glucose changes are more drastic under intraoperative stress and there is a different degree of lag in glucose concentration changes in interstitial fluid than in blood, whether CGM based on interstitial fluid can accurately and effectively guide intraoperative glucose management still needs to be validated by high-quality prospective studies.

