### Intervention description {11a}

#### Blood glucose management

Blood glucose monitoring

Intraoperative glucose monitoring is performed in both groups using CGM (Guardian RealTime, Medtronic, USA) in combination with arterial blood gas. A disposable glucose monitoring probe will be placed in the patient's upper arm by the investigator 6 h before surgery and connected to the monitoring system.

In the CG group, intraoperative ABG testing will be performed if the CGM value is < 6.1 mmol/L or > 10.0 mmol/L, or the rate of change of CGM value > 1.67 mmol/(L·min). Blood glucose adjustment will be performed according to the arterial blood glucose value.

In the G group, CGM monitoring results were blinded to patients and investigators. Intraoperative arterial blood gas checks will be performed every 2 h, and blood glucose adjustments will be made based on blood glucose results, and the frequency of blood gas tests will be adjusted as needed. CGM is used to record intraoperative glucose data only.2)Blood glucose management target: The intraoperative blood glucose management target is 7.8 ~ 10 mmol/L in both groups.3)Blood glucose-lowering measures: see Table 1 for the intraoperative glucose management measures for patients in both groups.

**Table 1 Tab1:** Blood glucose intervention

Perioperative target blood glucose: 7.8 ~ 10 mmol/L • If ABG-derived blood glucose > 10 mmol/L measured for the first time, start insulin infusion Insulin dose and mode of administration: • Loading dose: 0.1 U/kg, I.V Maintenance dose: (blood glucose value/5)U/h, infusion			
**Blood glucose (mmol/L)**	**If BG increased from previous measurement**	**BG decreased from prior measurement by ≤ 1.67 mmol/L**	**BG decreased from prior measurement by > 1.67 mmol/L**
**> 13.4**	Increase rate by 3U/h	Increase rate by 3U/h	No change in rate
**11.7 ~ 13.4**	Increase rate by 2U/h	Increase rate by 2U/h	No change in rate
**10.0 ~ 11.7**	Increase rate by 1U/h	Increase rate by 1U/h	No change in rate
**7.8 ~ 10.0**	No change in rate	No change in rate	No change in rate
**6.1 ~ 7.8**	No change in rate	Decrease rate by 50%	Hold insulin infusion
**5.5 ~ 6.1**	• Hold insulin infusion • Check BG every 2 h • Restart infusion if BG > 10 mmol/L		
**3.9 ~ 5.5**	• Hold insulin infusion • Check BG every 30 min until BG > 5.5 mmol/L, resume BG checks every 2 h • Restart infusion at 1/2 the prior infusion rate if BG > 10 mmol/L		

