#### Relevant concomitant care permitted or prohibited during the trial {11d}

A conventional anesthetic management protocol is used intraoperatively. In the absence of clear indications, the control group should avoid two blood glucose monitoring intervals of less than 2 h. ABG testing in the intervention group should be performed only when the blood glucose value monitored by CGM is < 7.8 mmol/L or > 10.0 mmol/L, or the rate of change is > 1.67 mmol/(L- min).

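### CGM accuracy is tested only in the CG arm, where a reference ABG is drawn essentially only after CGM has left its limits, so in-range CGM readings go practically unverified while the control arm's pairs are left out

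*Protocol article*

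**What the plan says.** Accuracy is a secondary outcome (Outcomes {12}). Statistical methods {20a} fixes its population: "the accuracy of CGM monitoring will be tested simultaneously for patients in the CG group". The same section sets the verdict: a mean relative error of at most 17% together with at least 95% of pairs in Clarke zones A and B.

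For the CG group, Blood glucose management under {11a} states that "intraoperative ABG testing will be performed if the CGM value is < 6.1 mmol/L or > 10.0 mmol/L", or when the CGM rate of change exceeds 1.67 mmol/(L·min). Section {11d} is restrictive and has another lower limit: "ABG testing in the intervention group should be performed only when the blood glucose value monitored by CGM is < 7.8 mmol/L", or on the same upper limit or rate.

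For the control group, {11a} says "Intraoperative arterial blood gas checks will be performed every 2 h", with the frequency then adjusted on the results. CGM is worn there too ("Intraoperative glucose monitoring is performed in both groups using CGM"), its results are blinded, and "CGM is used to record intraoperative glucose data only". Outcomes {12} takes the primary outcome from each participant's CGM data.

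**The concern.** An accuracy study needs reference values obtained without regard to the test result. In the CG arm the test result decides whether a reference exists, which is verification bias in its usual form. For a strategy that lets CGM decide when to look at blood glucose, the failure of most interest is a reassuring CGM value with blood glucose out of range. In the arm chosen, that failure draws no ABG and so leaves almost no trace in the data. The Background names interstitial lag as an open question, and lag could produce this kind of error.

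The control arm offers what the CG arm lacks, a blinded CGM and ABG draws that do not depend on it, yet {20a} leaves it out. An accuracy verdict worded for intraoperative CGM in general would then rest on a selected part of the readings.

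**Working it through.** **Step 1: does the rate trigger fill the gap?** Inputs: 1.67 mmol/(L·min) from {11a} and {11d}; the Background says that CGM "automatically detects glucose levels from interstitial fluid or blood every 5 min". Assuming that the rate is taken between consecutive readings, the change needed is 1.67 × 5 = 8.35 mmol/L. The untriggered band is only 10.0 - 6.1 = 3.9 mmol/L wide, or 10.0 - 7.8 = 2.2 mmol/L. A reading now in range fires the trigger only if the previous one was
- below 10.0 - 8.35 = 1.65 mmol/L, or
- above 6.1 + 8.35 = 14.45 mmol/L (limit 6.1) or 7.8 + 8.35 = 16.15 mmol/L (limit 7.8).

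It adds practically no in-range pairs.

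**Step 2: how much goes unpaired?** The article gives no glucose or error distribution, so these are assumptions: lognormal glucose, mean 10 mmol/L, CV 30% or 40%; CGM = glucose × (1 + bias + normal error), error SD 10%, 15% or 20%, bias -10%, 0 or +10%. A pair exists only if CGM is below the lower limit or above 10.0. This gives 18 settings for each limit, with out-of-range blood glucose defined by the trigger's own limits.

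| Lower limit (mmol/L) | Readings with no pair | Out-of-range blood values behind an untriggered CGM |
|---|---|---|
| 6.1 | 37-55% | 8-31% |
| 7.8 | 22-31% | 10-21% |

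One setting written out (CV 30%, error SD 20%, no bias, limit 6.1): 55.4% of readings trigger an ABG, so 100 - 55.4 = 44.6% do not. Of those, 24.7% are falsely normal, which is 0.446 × 24.7 = 11.0% of all readings, and 21.9% of all out-of-range blood values.

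**Step 3: does the selection shift the mean error?** The formula in {20a} is signed: (ABG - CGM)/ABG × 100%, with no absolute value. In the setting above it averages about 0% over all readings and -3.5% over triggered pairs, so both meet 17%. Read instead as absolute error, the figures are 16.0% and 17.5%. That is the only one of the 36 combinations (18 settings × 2 limits) that crosses 17%, and there the selection fails the device.

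**Step 4: would the Clarke criterion expose the misses?** In a second set of assumptions (mean 9-10 mmol/L, SD 2.5-3.8, error SD 15-20%, bias -15% to +15%), A+B among triggered pairs was 98.4-99.9%. Meanwhile 14-37% (limit 6.1) or 38-57% (limit 7.8) of in-range CGM readings were falsely normal. A+B over all readings was also above 98%, so the 95% rule is insensitive to this failure, and a direct count is needed.

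**Step 5: what could the control arm supply?** Assuming operations of 6 to 12 h with ABG at 0, 2, 4 ... h, there are 4 to 7 draws per patient. With 90 patients that is 90 × 4 = 360 to 90 × 7 = 630 pairs, none selected on CGM.

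**The case against.** Four points can be made against this.

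- **Some in-range pairs will exist.** Table 1 applies to both groups and orders timed rechecks after low ABG values; some will coincide with an in-range CGM. This stands, although Table 1 and the restrictive wording of {11d} conflict and must be reconciled. A reader might infer that in-range readings are never checked; the documents support only practically never.
- **Most misses lie close to a limit.** This also stands: of blood values above 13.4 or below 3.9 mmol/L, only 0-11% (limit 6.1) or 0-9% (limit 7.8) sit behind an in-range CGM in the Step 2 settings.
- **The control pairs are neither certain nor purely clock-timed.** Study setting {9} describes the control group as monitored by ABG alone, and Anesthesia management mentions probe placement only for the CG group. The Abstract and {11a} put CGM in both arms, and the primary outcome requires it. ABG frequency in the control arm also adapts to the previous ABG result, so disturbed periods may be over-sampled. The pairs are free of selection on CGM, but not of selection on glucose level.
- **Mean glucose and event rates.** A reader might infer that these are distorted as well, because ABG timing differs by arm. The article does not say whether they come from ABG or CGM, so that inference has no footing.

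**Conclusion.** The concern holds as a gap in coverage. The accuracy analysis is confined to the arm in which CGM selects its own reference values, and its pass rule says almost nothing about in-range readings. This is so with either lower limit. The sizes in Step 2 depend wholly on the assumed distributions and should be read as orders of magnitude.

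A reader might go further and infer that the selection flatters CGM or would overturn the 17% verdict. That is not supported: the shift in mean error is usually small, goes either way, and does not cross the limit under the signed formula as printed in the example worked above. Accuracy is a secondary outcome, so this is a change that should be made; it does not undermine the primary comparison.

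**What to change.** 1. In {20a}, make the control arm's pairs (blinded CGM against ABG) the primary accuracy set. State that ABG frequency there adapts to the previous ABG result, so the pairs are not selected on CGM but are not purely clock-timed.
2. From that set, report the share of in-range CGM readings whose paired ABG is out of range, alongside the mean relative error and the Clarke grid.
3. Report the CG arm's triggered pairs separately, as secondary.
4. Reconcile {9} and Anesthesia management with the Abstract, {11a} and {12} on whether control patients wear CGM. Reconcile the lower limit of 6.1 mmol/L (Abstract, {11a}) with 7.8 mmol/L ({6b}, {11c}, {11d}); which limit applies is for the investigators to settle.

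If CGM is recorded in both arms, as the primary outcome needs, the cost is a change of analysis wording and some tabulation, with no extra sampling and no change in care. If it is not, this remedy is unavailable and the accuracy claim should be limited to readings that triggered an ABG.

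### CGM accuracy is judged from repeated, mostly alarm-triggered pairs in the CG group, using a Pearson correlation and pooled point estimates with no stated uncertainty

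*Protocol article*

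**What the plan says.** The section on statistical methods for primary and secondary outcomes {20a} restricts the assessment to one arm: "the accuracy of CGM monitoring will be tested simultaneously for patients in the CG group". It names three tools. The first is correlation: "Pearson linear correlation analysis will be applied to determine the correlation between CGM- and ABG-derived glucose levels". The second is the Clarke error grid. The third is the relative difference between ABG and CGM, which "will be applied to calculate the overall clinical mean relative error". Accuracy is then decided by a rule with two parts. The mean relative error has an upper limit of 17%, and the pooled share of points in Clarke zones A+B has a lower one: if this "is not less than 95% of the total, the accuracy will be judged to be satisfactory". Pearson's r is not part of that rule. The section describes no per-patient summary, within-patient term or interval for these quantities.

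The pairs arise under the monitoring rules. Blood glucose management states: "In the CG group, intraoperative ABG testing will be performed if the CGM value is < 6.1 mmol/L or > 10.0 mmol/L", with a rate-of-change trigger as well. The section on concomitant care {11d} is restrictive: "ABG testing in the intervention group should be performed only when" the CGM is outside its limits or changing fast, with a lower limit of 7.8 mmol/L instead of 6.1. Section {33} says that the number of blood samples varies with the length of the operation and with glucose changes. In the control arm, ABG is taken every 2 h while a blinded CGM records.

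**The concern.** Three features meet in this analysis. First, a correlation is listed as an accuracy method although it cannot see bias: if CGM were exactly 0.7 × ABG, r would be 1. Second, the device under test largely chooses the moments at which it is tested. When the CGM reads in range and arterial glucose does not, usually no pair exists. Third, each patient gives several pairs, in unequal numbers, and the rule works on the pooled total, so a patient with many alarms counts more than one with few.

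At stake is the published statement on whether CGM is accurate in major surgery. The Background presents this as still to be validated, and the Outcomes section lists it as a secondary outcome. A bare satisfactory or unsatisfactory verdict from such pairs does not say which readings it describes or how firm it is.

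**Working it through.** The plan has no computed figure to reproduce here; 17% and 95% are criteria. The document gives 90 patients per group. It gives no pair counts, mean or SD of intraoperative glucose, sensor error or within-patient correlation (ICC). Those are assumed below, and a range is shown.

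**1. Effect of alarm selection on r and on the error.** I simulated 400,000 independent pairs with glucose SD 2 mmol/L and an unbiased sensor with 17% random error (an SD, not the protocol's 17% limit). I compared all readings with only those where CGM lies outside the alarm limits, ignoring rate alarms and rechecks.

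| Mean glucose (mmol/L) | r, all | r, outside 6.1–10 | r, outside 7.8–10 | Mean absolute relative error: all / 6.1–10 / 7.8–10 |
|---|---|---|---|---|
| 9 | 0.79 | 0.86 | 0.84 | 13.5% / 15.6% / 14.9% |
| 11 | 0.73 | 0.68 | 0.75 | 13.6% / 13.1% / 13.8% |
| 13 | 0.67 | 0.61 | 0.64 | 13.6% / 12.4% / 12.8% |

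Both quantities can move either way. The formula as printed is signed. On that reading, the mean error of this unbiased sensor shifts from 0 to −4.2% at mean 9 with the 6.1–10 limits, and to −0.2% with 7.8–10. The quantity set against 17% thus depends partly on the alarm rule, which the protocol gives in two versions.

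A second simulation followed 90 patients for 8 h, with alarm-triggered ABG at most every 30 min. With small glucose SD and the 6.1/10 trigger, alarm-selected against 2-hourly r was 0.96 against 0.86 at mean 8, but 0.74 against 0.83 at mean 9.

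**2. Weighting.** In that second simulation the 10% of patients with most pairs supplied 10% to 38% of all pairs. With the 7.8/10 trigger this was 10% to 17%; the high shares came only with tight glucose and the 6.1/10 trigger.

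An assumed example shows that weighting can matter: 81 patients with 4 pairs at 97% A+B, and 9 patients with 20 pairs at 85%.
- Pooled: (81×4×0.97 + 9×20×0.85) / 504 = 467.28 / 504 = 92.7%, a fail.
- Patient-weighted: (81×0.97 + 9×0.85) / 90 = 86.22 / 90 = 95.8%, a pass.

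**3. Precision.** Design effect = 1 + ((1 + cv²)m − 1) × ICC, with m pairs per patient and cv the coefficient of variation of the pair counts. Take m = 4 to 10, ICC = 0.1 to 0.5 and cv = 0 to 1.
- Smallest: 1 + 3 × 0.1 = 1.3. Largest: 1 + 19 × 0.5 = 10.5.
- The pairs number 90×4 = 360 to 90×10 = 900. Their effective number runs from 360/4.5 = 80 to 900/1.9 = 474.
- The 95% half-width around 96% is 1.96 × √(0.96×0.04/n). For n = 900 and 360 this is 1.3 and 2.0 points. For n = 474 and 80 it is 1.8 and 4.3 points.

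Over the whole clustered range, an observed 96% could not be told apart from the 95% limit.

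**The case against.** Much can be said for the plan. Pearson's r is outside the pass rule, and the section assigns consistency to the Clarke grid. A reader might infer that a sensor reading 30% low could pass on a high correlation. It could not: its mean relative error is 30%, and it fails the 17% criterion. Nor would its r be near 1 with noise: 0.7 × ABG with 17% random error gives r = 0.79, and about 6% error is needed to reach 0.96.

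A reader might also infer that the correlation is inflated. The table shows r rising or falling with a mean glucose that the document does not state. Another tempting inference is that the verdict hangs on a few unstable patients. That rests on the assumed 81-and-9 example; strong concentration appeared only in some scenarios, and in that example pooling makes the rule stricter.

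No p-value or interval is planned for accuracy, so none can be called too narrow. Treating pairs as independent is an inference from the pooled wording, and a fuller plan may handle clustering. Finally, CG pairs do not arise only from out-of-range readings: rate-of-change alarms and the Table 1 rechecks add others.

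All these limits stand. What remains is that the article itself fixes the arm, the correlation, the pooled criteria and a verdict on point estimates, for pairs that its own rules make repeated and largely device-selected.

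**Conclusion.** The point holds as a minor one. Pearson's r adds nothing on agreement. The CG-only pairs under-represent in-range readings and give more weight to patients with more alarms, and the verdict comes without a statement of its uncertainty. The direction of the effect on r, on the error or on the verdict cannot be settled from the document. The half-width of 1.8 to 4.3 points rests on the assumed pair counts and ICC. Severity is minor because this is one secondary outcome and the pass rule does not use the correlation.

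**What to change.** - Replace Pearson's r, or keep it as description only, and report Bland-Altman bias with 95% limits of agreement for repeated measurements, from a model with a random patient effect.
- Give 95% intervals from a bootstrap that resamples patients, for the mean relative error and the A+B share.
- State in advance whether the pooled or the patient-weighted value decides the verdict, and report the other as a sensitivity analysis. Otherwise the verdict is undefined when the two disagree.
- Add the control arm's scheduled 2-hourly ABG values paired with the blinded CGM record. Modelling the CG pairs cannot restore in-range pairs that were never taken; these can supply some. They are less alarm-selected, though not free of selection, because control-arm frequency may be adjusted after a result.
- Reconcile the two lower alarm limits (6.1 and 7.8 mmol/L), since they determine which pairs exist.

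The cost is revised wording, a little more analysis and somewhat wider intervals. No new data are needed, provided control patients wear the sensor, as the blood glucose monitoring text and the primary outcome require.
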